**Methods:**

In this study, we plan to include 186 patients who have undergone modified Milligan-Morgan hemorrhoidectomy, which only sutured external hemorrhoids to reduce the risk of bleeding. The purpose is to determine whether the use of nonpressure dressings after open hemorrhoidectomy is inferior to the use of pressure dressings in terms of severe postoperative bleeding and postoperative complications. The primary endpoints of the trial are the incidence of urinary retention within 24 h after surgery and the incidence of severe postoperative bleeding 1 h after dressing removal, which requires revision surgery within 24 h after the surgery. The secondary endpoints of the study are the pain score, anal distension score, postoperative use of analgesics, and incidence of medical adhesive-related skin injury, all of which will be assessed before removing the dressings. The length of hospitalization in days and hospitalization expenses will be recorded. Safety will be assessed with consideration of all adverse and severe adverse events related to the study treatment.

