#### Secondary outcome measures

Postoperative pain will be measured at rest with routine care at 6, 18, and 25 h by using a visual analog scale (VAS) after the surgical procedure. The scale will range from 0 to 10 points, with higher scores indicating more severe pain [21]: 0 = no pain, 1~3 = slight pain that can be tolerated, 4~6 = pain that can be tolerated but affects sleep, and 7~10 = unbearable pain that affects not only appetite but also sleep.The change in hemostatic effect scores within 25 h will be the other primary outcome. The effect of hemostasis will be graded using a 3-point ordinal scale: 0 = the dressing was not soaked before removal, 1 = there was no bleeding after changing the dressing due to excessive blood oozing, and 2 = postoperative bleeding requiring surgical revision occurred.The change in mean rectal tenesmus sensation scores within 25 h will be graded using a 3-point ordinal scale: 0 = no abnormal sensation; 1 = mild anal discomfort, occasionally abnormal sensation; 2 = strong foreign-body sensation; and 3 = strong foreign body sensation that is not easily relieved after rest or treatment.The incidence of medical adhesive-related skin injuries will be measured. The skin condition will be assessed by a senior wound specialist nurse. If there is no skin damage, “no” will be recorded. When any of the following situations occur, “yes” will be recorded: (1) exfoliation, (2) tension blisters, (3) skin lacerations, (4) contact dermatitis, and (5) allergic dermatitis. In the statistical analysis, the incidence of medical adhesive-related skin damage will be calculated by a statistician.The change in the mean anal edema score when the dressing is removed 24 h after surgery will be graded using a 4-point ordinal scale: 0 = no anal edema, 1 = mild edema (< 1/4 anal area ), 2 = moderate edema (1/4 to 1/2 anal area ), and 3 = severe edema (> 1/2 anal area ).The total dose of analgesics before removing the dressing will be recorded.The length of hospitalization will be recorded in days.Hospitalization expenses will be recorded.

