### Statistical analysis

The validity analysis of the study will be mainly based on intention-to-treat (ITT, all randomized cases) and per-protocol analyses (PP, cases that comply with the trial protocol, good compliance, and completed CRF). First, the Shapiro-Wilk test will be used to test whether the quantitative data follow a normal distribution. If the data are normally distributed, the mean value and standard deviation will be used to describe the quantitative data, and a *t* test will be used for analysis. Nonnormally distributed data will be expressed as the median and quaternary and compared using the Mann-Whitney *U* test. The qualitative data will be expressed as the frequency and percentage; non-grade data will be compared by the chi-square test, and grade data will be compared by the Mann-Whitney *U* test. Randomization will be performed 24 h prior to the surgical intervention. Data will not be collected and analyzed for patients not undergoing surgical intervention. If the scheduled surgery is not performed, the study participant will be excluded from the clinical trial. For every patient who is excluded from the trial after randomization and before the start of the observation period (postoperative wound with or without compression), another study participant will be included to achieve the number of cases needed. The randomization sequence will continue. The next patient will not necessarily be assigned to the same group as the excluded patient. This research will continue until the required number of evaluable patients is reached. Due to complications, a very small number of patients may not be able to comply with the randomly assigned treatment. The study will not exclude these patients. All statistical tests will be two-sided, and *P* < 0.05 will be considered statistically significant. If baseline factors are inconsistent between the two groups, subgroup analysis and multivariate analysis will be considered.

In the safety analysis, Fisher’s exact test will be used to compare the incidence of AEs and SAEs by category (severity) between the two groups.

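### If the 0-1-2 hemostatic score is the bleeding primary, the Mann-Whitney rule for graded data does not test the stated question, severe bleeding requiring revision surgery

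*Protocol article*

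**What the plan says.** The Abstract (Methods) says the trial asks whether nonpressure dressing "is inferior to the use of pressure dressings in terms of severe postoperative bleeding and postoperative complications". It gives the bleeding endpoint as "the incidence of severe postoperative bleeding 1 h after dressing removal, which requires revision surgery within 24 h after the surgery", which is a yes/no incidence.

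The outcomes section words it differently. Under Secondary outcome measures it states: "The change in hemostatic effect scores within 25 h will be the other primary outcome". It continues: "The effect of hemostasis will be graded using a 3-point ordinal scale". The lower grades are "0 = the dressing was not soaked before removal, 1 = there was no bleeding after changing the dressing due to excessive blood oozing"; the top grade is "2 = postoperative bleeding requiring surgical revision occurred". Only grade 2 is therefore the event named in the abstract.

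Objectives {7} differs again. It names urinary retention as the only primary objective and lists the hemostatic score among the secondary ones.

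Statistical analysis has one general rule for categorical outcomes: "non-grade data will be compared by the chi-square test, and grade data will be compared by the Mann-Whitney" U test. It does not name the hemostatic score, but a graded ordinal scale falls under the second half of the rule. All tests are two-sided at 0.05.

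The Background calls active bleeding within 24 h very low and gives no figure. No rate of oozing appears anywhere.

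**The concern.** A Mann-Whitney test of the score compares the whole 0/1/2 distribution between arms. The stated question concerns grade 2 alone. If most patients are grade 0 and very few are grade 2, most of the rank information lies in grade 0 against grade 1, that is, whether a dressing was changed for oozing.

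The two arms use different materials (foam adhesive dressing over gauze, or a taped gauze tower). A difference in soaking unrelated to severe bleeding is therefore plausible.

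At stake is the safety conclusion on leaving out the pressure dressing. A P value labelled as the primary bleeding result could be read as evidence on severe bleeding when it mainly reflects dressing changes.

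**Working it through.** **Inputs.** From the protocol: 93 per arm, two-sided 0.05, the three grade definitions and the Mann-Whitney rule. Assumed, because the protocol gives none: all grade 1 and grade 2 frequencies.

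**The plan's own figure.** The only design calculation is for urinary retention (44.7% v 24.7%, 80% power). The unpooled two-proportion formula gives 85 per arm, and 85 × 1.1 = 93.5, close to the stated 93. Nothing is calculated for bleeding, so this neither supports nor weakens the point.

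**Rank weights.** With pooled proportions p0, p1, p2, the midrank step (as a fraction of N) is (p0 + p1)/2 from grade 0 to 1 and (p1 + p2)/2 from grade 1 to 2.
- 78/20/2%: (0.78 + 0.20)/2 = 0.49 and (0.20 + 0.02)/2 = 0.11.
- 95/3/2%: 0.49 and 0.025.

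The second step is small whenever grade 0 is frequent and grade 2 rare, whatever the oozing rate.

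**Worked tables** (arm A v arm B, counts in grades 0/1/2, N = 186). The expected rank sum for A is 93 × 187/2 = 8695.5. The tie-corrected variance is (93 × 93/12) × [187 − Σ(t³ − t)/(186 × 185)], where t is the pooled count in each grade.

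1. *Equal re-operations, 63/28/2 v 82/9/2.* Midranks are 73, 164 and 184.5. Rank sum A = 63 × 73 + 28 × 164 + 2 × 184.5 = 9560, which is 864.5 above expectation. SD 264.3, z = 3.27, p = 0.001. Fisher's exact test on grade 2 (2 v 2): p = 1.0.
2. *More re-operations in A, less oozing, 78/10/5 v 64/28/1.* Midranks are 71.5, 161.5 and 183.5: 90 ranks from grade 0 to 1, but 22 from grade 1 to 2. Rank sum A = 8109.5, which is 586 below expectation. SD 271.4, z = −2.16, p = 0.031 in favour of A, the arm with 5 re-operations against 1. Fisher on grade 2: p = 0.21.
3. *Excess of re-operations offset by less oozing, 73/12/8 v 73/20/0.* Midranks are 73.5, 162.5 and 182.5. Rank sum A = 8775.5, which is 80 above expectation. SD 262.5, z = 0.30, p = 0.76. Fisher on grade 2 (8 v 0): p = 0.007.

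**How often, under assumed rates** (100,000 simulated trials per row, 93 per arm):

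| Oozing A v B | Re-operation A v B | Mann-Whitney significant | Fisher on grade 2 |
|---|---|---|---|
| 30% v 10% | 2% v 2% | 91%, against A | 0.4% |
| 30% v 20% | 2% v 2% | 32%, against A | 0.4% |
| 6% v 3% | 2% v 2% | 12%, nearly all against A | 0.4% |
| 10% v 30% | 5% v 1% | 66%, in favour of A | 16% |
| 20% v 40% | 5% v 1% | 54%, in favour of A | 16% |
| 25% v 15% | 5% v 1% | 66%, against A | 16% |
| 25% v 25% | 10% v 1% | 38%, against A | 72% |
| 5% v 5% | 5% v 1% | 18%, nearly all against A | 16% |
| 25% v 25% | 3% v 1% | 7%, mostly against A | 3% |

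With 84 per arm, roughly the number left after 10% dropout, the pattern is the same: 88% instead of 91% in the first row and 62% instead of 66% in the fourth.

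**The case against.** **The protocol does not tie Mann-Whitney to severe bleeding.** This stands in part. The abstract's endpoint is an incidence, and the same rule would send it to the chi-square test. The rank test follows only if the outcomes section's definition governs, and the objectives list the score as secondary. The sections disagree, so the point is conditional on that. It does not disappear, because the outcomes section expressly calls the score primary and no other stated rule fits a graded scale.

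**Severe bleeding is compared elsewhere.** Adverse events {22} names severe hemorrhage as a known event, and adverse events are compared by Fisher's exact test. This mitigates in part. That comparison is by severity category and limited to treatment-related events, so it is not a direct comparison of revision surgery and does not correct a misleading primary P value.

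**A rank test suits an ordinal hemostasis score.** True. A significant result when oozing differs is a valid statement about hemostasis. The mistake would be to read it as a statement about severe bleeding.

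**Oozing may be uncommon, and the reversal needs opposite movements.** Both are fair. Sutured external incisions, preventive hemocoagulase in both arms and complete hemostasis before dressing make low oozing plausible. In the reversal, one arm must have more re-operations yet clearly less oozing. If both move the same way (25% v 15% with 5% v 1%), the rank test rejects against the worse arm far more often than Fisher on grade 2.

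**The analysis plan may settle it.** Tabulations and intervals can be left to that plan. The objection here is to definitions and a rule that the protocol itself states.

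**Conclusion.** The point holds conditionally. If the 0-1-2 score is the bleeding primary, its Mann-Whitney test cannot carry a conclusion on severe bleeding. When oozing differs between arms, the test can be significant with equal re-operations, can favour the arm with more of them, or can miss an excess. The worked tables show each case at the planned size (p = 0.001, 0.031 and 0.76). These show what can happen; they do not forecast this trial, because every oozing and re-operation rate is assumed.

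Two stronger readings are tempting and not supported:
- *That oozing is common here.* The documents give no rate. The small step from grade 1 to grade 2 does not need one, but the size of the effect depends on how far oozing differs between arms.
- *That the rank test generally has much less power against re-operations.* It does at 10% v 1% with 25% oozing (38% v 72%). At 5% v 1% with 5% oozing the two tests are about level (18% v 16%), and at 3% v 1% with 25% oozing neither is informative (7% v 3%). With no oozing at all and re-operations of 4 against 0, Mann-Whitney gives p = 0.044 and Fisher p = 0.12.

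**What to change.** Reconcile the Abstract, Objectives {7}, the outcomes section and Statistical analysis so that they name one bleeding endpoint with one status. Then state in Statistical analysis that:
- the severe-bleeding conclusion rests on the proportion with grade 2 (revision surgery), compared by the risk difference with its confidence interval and an exact test;
- grade 1 (dressing change for oozing) is reported separately as its own proportion;
- any Mann-Whitney test of the 0/1/2 score is a supportive analysis of hemostasis and supports no conclusion on severe bleeding.

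This needs a few sentences and no new data. The cost is visible imprecision. At an assumed 2% in each arm, the 95% half-width for the difference is 1.96 × √(2 × 0.02 × 0.98/93) = 0.040, about ±4 percentage points (4.2 with 84 per arm). That reflects what 186 patients can say about a rare event, and reporting it openly is preferable to a rank-test P value that answers a different question.

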## Introduction

### Background and rationale {6a}

As people’s personal and work lifestyles change, the incidence of mixed hemorrhoids in China is increasing annually [1]. According to an epidemiological study, in 2016, the incidence of anorectal diseases among urban residents in China was 51.14%, and the incidence of mixed hemorrhoids was the highest among these diseases, accounting for 50.28% of all anorectal diseases [2]. In the USA, the incidence is approximately 4%, with the prevalence being highest between 45 and 65 years of age [3]. It is estimated that about 50% of Germans have symptomatic hemorrhoids, and some authors believe that up to 70% of people are affected by hemorrhoids [4]. Mixed hemorrhoids can occur at any age, and the symptoms include itching, pain, bleeding, swelling, prolapse of an anal tumor, foreign body sensation, etc. [5]. Although mixed hemorrhoids are not fatal or malignant, these symptoms can reduce a patient’s quality of life and have negative psychological and physical effects [6]. The treatment types include conservative treatment and surgical treatment. Mixed hemorrhoids with mild symptoms can be treated conservatively [7]. However, surgery is the initial treatment of choice in patients with symptomatic grade III–IV hemorrhoids [5, 6, 8]. Various surgical procedures have been used to treat symptomatic hemorrhoids in recent years, but (Milligan-Morgan) ligation is still considered the standard surgical procedure [9–13]. At the end of the operation, the wound is bandaged by a pressure dressing, which is the most traditional type of dressing that has been used clinically for many years [14]. The main purpose of pressure bandaging is to stop bleeding, but it may increase the incidence of postoperative complications, such as urinary retention, pain, anal swelling, and medical adhesive-related skin damage [12, 15–18]. Besides, clinical observation shows that with medical advances and the application of hemostatic drugs, the incidence of active bleeding within 24 h after modified Milligan-Morgan hemorrhoids surgery is very low. In addition, the necessity of pressure dressing after hemorrhoidectomy has received little scientific attention. A previous controlled trial included 67 patients who underwent Milligan-Morgan hemorrhoidectomy [19]. The data indicated that the use of a nonpressure dressing after hemorrhoidectomy reduces the incidence of urinary retention and catheterization. However, the incidence of severe postoperative bleeding and other postoperative complications was not assessed. There is no consensus on whether it is necessary and beneficial to use a nonpressure dressing after hemorrhoidectomy. The results of this randomized clinical study will preliminarily help answer this question.

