### Adverse events (AEs) {22}

In this study, AEs are defined as any treatment-related medical events, including any treatment-related adverse and unexpected signs, symptoms, or diseases. The AEs known to follow nonpressure dressing and pressure dressing treatment include severe postoperative hemorrhage. At each visit, the participants will report AEs and be examined by a physician. AEs will be evaluated and reported to the principal investigator according to Common Terminology Criteria for Adverse Events (v4.03) [22].

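### Bleeding that needs revision surgery falls under up to three different significance tests, and the plan does not say which result governs

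*Protocol article*

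**What the plan says.** All references are to the protocol article.

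- **Abstract, Methods.** The second of two primary endpoints is "the incidence of severe postoperative bleeding 1 h after dressing removal, which requires revision surgery". This is a yes/no outcome.
- **Primary objectives and Secondary objectives.** Only urinary retention is listed as primary. The hemostatic effect score appears among the secondary objectives.
- **Secondary outcome measures.** The hemostatic effect score is called the other primary outcome, although it stands under the secondary heading. "The effect of hemostasis will be graded using a 3-point ordinal scale", and grade 2 means that "postoperative bleeding requiring surgical revision occurred".
- **Adverse events (AEs) {22}.** "The AEs known to follow nonpressure dressing and pressure dressing treatment include severe postoperative hemorrhage". AEs are limited to treatment-related events.
- **Statistical analysis.** For qualitative data, "non-grade data will be compared by the chi-square test" and "grade data will be compared by the Mann-Whitney" *U* test. In the safety analysis, Fisher's "exact test will be used to compare the incidence of AEs and SAEs by category (severity) between the two groups". Every test is two-sided at P<0.05.
- **Background and rationale {6a}.** The authors expect few events: "the incidence of active bleeding within 24 h after modified Milligan-Morgan hemorrhoids surgery is very low". No rate is given.

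**The concern.** One clinical event has three roles, and the general rules of the Statistical analysis section give each role its own test. All three tests use the same threshold, and no sentence ranks them. With few events these tests can fall on opposite sides of 0.05.

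The Abstract asks whether nonpressure dressing is inferior on severe bleeding, so this is the main safety question. With five re-operations against none, a report could truthfully say either that bleeding was significantly more frequent or that AEs did not differ significantly. The plan would support both statements, and the choice could be made after the counts are known.

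**Working it through.** **Inputs.** From Sample size {14}: 93 per arm and alpha 0.05. Two-sided testing is from Statistical analysis. The document gives no bleeding rate, so the rates below are assumptions shown over a range.

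**The plan's own figure.** The sample size rests on urinary retention (44.7% v 24.7%, 80% power), with unpooled variance:

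n = (1.960 + 0.842)² × (0.447×0.553 + 0.247×0.753) / 0.200² = 85 per arm

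85 × 1.1 = 93.5, cut to 93, so 186 in total. The figure is reproduced. It serves here only as the arm size.

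**One table by each route: 5 v 0 events, 93 per arm.**

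- Uncorrected Pearson: χ² = 186 × (5×93)² / (93×93×5×181) = 5.14, P=0.023.
- Yates-corrected: χ² = 186 × (5×93 − 93)² / (93×93×5×181) = 3.29, P=0.070.
- Fisher: 2 × (93×92×91×90×89) / (186×185×184×183×182) = 2 × 0.0296, P=0.059.
- Mann-Whitney on the 0/1/2 score, no grade 1 patients: P=0.024. With an assumed 10 grade 1 patients per arm: P=0.24, because the test then no longer isolates revision bleeding.

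**Other small tables, 93 per arm.**

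| Events | Pearson | Yates | Fisher |
|---|---|---|---|
| 4 v 0 | 0.043 | 0.129 | 0.121 |
| 5 v 0 | 0.023 | 0.070 | 0.059 |
| 7 v 1 | 0.030 | 0.071 | 0.065 |
| 9 v 2 | 0.030 | 0.062 | 0.058 |
| 10 v 3 | 0.044 | 0.084 | 0.081 |
| 11 v 3 | 0.026 | 0.052 | 0.048 |

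In the first five rows uncorrected Pearson is significant and Fisher is not, while Yates agrees with Fisher. With up to 3 events in the smaller arm, 11 v 3 is the only table found where Yates and Fisher disagree. With 84 per arm (93 less about 10%) the verdicts are the same; for example, 5 v 0 gives 0.023 v 0.059.

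**How often uncorrected Pearson and Fisher disagree at 0.05** (binomial probabilities summed over all discordant tables, 93 per arm):

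| Assumed true rates | Probability of opposite verdicts |
|---|---|
| 5% v 1% | 18% |
| 4% v 1% | 15% |
| 2% v 1% | 4.4% |
| 1% v 1% | 1.1% |
| 1% v 0.5% | 0.9% |

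At equal true rates between 1% and 5% the probability is about 1% to 3.5%.

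**Unequal arms.** The Randomization and blinding section specifies simple randomization, so 93:93 is not assured. The SD of one arm's size is √(186 × 0.25) = 6.8, so 100:86 would be unremarkable. Take 5 events in the arm of 86 and none in the arm of 100:

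- Pearson: χ² = 186 × (5×100)² / (86×100×5×181) = 5.97, P=0.015.
- Yates: χ² = 186 × (500 − 93)² / (86×100×5×181) = 3.96, P=0.047.
- Fisher: (86×85×84×83×82) / (186×185×184×183×182), P=0.020. The opposite tail is more probable than the observed table and is not added.

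All three now fall below 0.05. The discordance figures above therefore hold only for equal arms.

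**The case against.** The strongest reply is that no sentence assigns the chi-square test to bleeding. A reader might infer from the Abstract that it does, but the section that sets out the outcomes uses an ordinal score, and graded data go to Mann-Whitney. This stands. The chi-square route is an inference from the Abstract's yes/no endpoint. It does not remove the conflict: Mann-Whitney and Fisher also split on 5 v 0 when no patient is grade 1.

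A reader might also infer that the plan is certain to produce two P values for an identical table. The text does not establish that. Fisher is applied by severity category to treatment-related AEs, so the counts may differ from those of the outcome. Differing counts would still need a statement of which analysis governs.

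The plan does not say whether the chi-square is corrected, and Yates removes the disagreement in most of the tables shown. This also stands. Such details, and fallbacks for small cells, are commonly left to the statistical analysis plan, which the article says exists and which is not shown; their absence is no finding. What remains is that the article itself gives one event several definitions and tests.

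Two further inferences fail. Uncorrected Pearson does not inflate type I error here: at true rates of 1% to 5% with equal arms its size is 1.1% to 4.5%. Nor does the point extend to adhesive skin injury, because the document gives no rate for it and does not suggest that it is rare.

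**Conclusion.** The point holds in a limited form. Revision bleeding is a yes/no primary endpoint, a grade of an ordinal primary outcome and an AE, with a different test for each and no governing result. Opposite verdicts are possible at the low counts that the authors expect.

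Their likelihood rests on three assumptions: an uncorrected chi-square (or Mann-Whitney with few grade 1 patients), equal arms, and the true rates. If bleeding is rare in both arms, opposite verdicts are uncommon, at about 1%. They become material, at 15% to 18%, only if one arm bleeds at 4% to 5% and the other at 1%. That is the situation in which the safety question would matter most.

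**What to change.** 1. Reconcile the Abstract, the Primary and Secondary objectives and the Secondary outcome measures on whether the bleeding endpoint is primary or secondary, and whether it is the yes/no event or the 0/1/2 score.
2. Name one governing exact test for revision bleeding wherever it is reported: Fisher, or a named unconditional exact test. Fix the choice before the data are seen, because it matters. Boschloo's test gives 0.047 for 5 v 0 when tables are ordered by the two-sided Fisher P, against Fisher's 0.059. Either choice ends the conflict.
3. State that the AE table is descriptive for this event.
4. Report the risk difference with a score 95% CI as the main result, so that the reading does not turn on which side of 0.05 a P value falls.

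The cost is wording in the outcome and analysis sections, submitted as an amendment. Sample size, data collection and conduct do not change.

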### Sample size {14}

The results of this study will be compared with the two-sided, two-sample chi-square test. The sample size should provide 80% statistical power at a significance level of 0.05, and a sample size ratio of 1:1. In the preliminary trial, the incidence of urinary retention was the main outcome measure and was 44.7% in the nonpressure dressing group and 24.7% in the pressure dressing group. Considering an anticipated dropout rate of 10%, we plan to include a total of 186 participants, with 93 participants per group.

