### Recruitment {15}

Researchers will recruit participants from the inpatient wards of Integrated Traditional Chinese and Western Medicine Departments. Patients eligible for the trial must meet all the inclusion criteria and exclusion criteria before enrollment. To recruit enough participants, all doctors in these departments will be informed of the trial and will be asked to contact the research assistant if they encounter potentially eligible patients. Potential participants will be screened, receive information on the trial, and then, be asked to sign informed consent forms. Patients who meet the selection criteria will undergo baseline assessments, and the eligible patients will be asked by medical staff to complete a general information form including their name, sex, age, medical history, etc.

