## Randomization and blinding

Randomization will be performed by an independent statistician with no clinical involvement in this trial by use of a random number generator program in Excel software (Kingsoft Office Software Co. Ltd., China). A simple randomization method and table of random numbers will be used. If the selected number is even, the patient is allocated to the nonpressure dressings group, and if it is odd, the patient is allocated to the pressure dressings group in a 1:1 ratio. Only one data administrator can access the random number table on the computer. An independent staff member who will not take part in the performance of this study will seal the random numbers in opaque envelopes. Then, the primary investigator will save these envelopes and open one of them when a participant is enrolled.

The participants will be enrolled by nursing staff and research assistants in the order of admission time. And they will be grouped by the data administrator using the table of random numbers. The two groups will use different types of dressings, and the operators will place the dressings. The patients can feel whether the wound is pressurized, so they cannot be blinded. However, the operators will remove the dressing before the observer’s follow-up. The observers and statisticians will be blinded to the group assignments.

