## Discussion

Pressure dressings are commonly used and have been considered a clinical standard for wounds after mixed hemorrhoid operations in China. However, these dressings can lead to some postoperative complications, and there are few reports on improvements in wound dressing methods after hemorrhoid surgery. This study will be carried out to determine whether nonpressure bandaging can be used routinely after open hemorrhoidectomy and whether it may be considered in specific circumstances.

During the operation, the patients will be treated with general anesthesia, and the method of applying a pressure dressing is complicated, so at least two medical staff will perform wound bandaging; nonpressure dressings need only a self-adhesive foam dressing, and only one medical staff member will be needed to perform wound dressing, and the process takes less time. The nonpressure dressing method can not only reduce the workload of medical staff but also save time.

Methods to minimize bias were implemented whenever possible. Randomization was performed 24 h before surgery. Randomization ensures a statistically consistent baseline between the experimental and control groups. However, one limitation of this study is that the researchers and patients cannot be blinded to the group assignments. The blinding of patients is an important way to prevent bias, but unfortunately, this step cannot be carried out in this study. However, the observers can be blinded. Before conducting any trial-related procedures, the researcher will obtain a written informed consent from each potential research participant. Randomization will be performed with a random number table generated in Excel, and then, the patients will be assigned a group according to the order of admission.

The research plan is consistent with clinical practice to the greatest extent possible to ensure complete and trouble-free data collection. Observation indicators such as pain and anal swelling may have affected the evaluation at certain time points while the patient is sleeping. Missing data are expected in these cases, but they should be minimized. The research leader will bear full legal responsibility for the entire study and publish the data on the website of the Clinical Research Management Department of West China Hospital of Sichuan University. Anyone who needs data can contact the author.

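### Adjusted and subgroup analyses hinge on an undefined, optional baseline-imbalance trigger, and their standing relative to the chi-square test is not stated

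*Protocol article*

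**What the plan says.** The protocol article's Statistical analysis section sets unadjusted tests as the default: "non-grade data will be compared by the chi-square test, and grade data will be compared by the Mann-Whitney" U test. The Sample size section agrees: "The results of this study will be compared with the two-sided, two-sample chi-square test". Covariates enter only through one conditional sentence: "If baseline factors are inconsistent between the two groups, subgroup analysis and multivariate analysis will be considered". No covariate, imbalance criterion, model or subgroup is named there.

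Three other places bear on it. Under Randomization and blinding, "A simple randomization method and table of random numbers will be used", with no stratification described. Under Recruitment, patients "complete a general information form including their name, sex, age, medical history, etc", so sex and age are on record before surgery. The Discussion asserts: "Randomization ensures a statistically consistent baseline between the experimental and control groups".

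**The concern.** Under correct randomization, baseline differences between arms are chance differences. Their observed size says nothing about whether a factor predicts urinary retention, so it is a poor basis for choosing covariates. A strong predictor that looks balanced would be left out, and an irrelevant factor that looks unbalanced could be put in.

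Subgroup analysis is no remedy either. It splits 186 patients into smaller comparisons and answers a different question, namely whether the effect varies between strata.

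The sentence also leaves three choices open: what counts as inconsistent, whether to act on it, and which result then leads. The Discussion's statement that randomization secures a consistent baseline fits poorly with a rule for when it does not, and simple randomization of this number of patients gives no such guarantee.

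At stake are the credibility of the urinary-retention result, if crude and adjusted analyses disagree, and possibly some power.

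**Working it through.** **Inputs from the protocol article (Sample size).** Retention "44.7% in the nonpressure dressing group and 24.7% in the pressure dressing group", as printed (the direction does not affect a two-sided calculation). "The sample size should provide 80% statistical power at a significance level of 0.05, and a sample size ratio of 1:1". Dropout is 10%, with 93 per group and 186 in total.

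**1. The plan's own figure.** With unpooled variance, n per arm = (1.960 + 0.842)² × (0.447×0.553 + 0.247×0.753) / 0.200² = 7.849 × 0.4332 / 0.04 = 85. Then 85 × 1.1 = 93.5, truncated to 93 per arm, or 186. The planned number therefore rests on an unadjusted comparison. After 10% dropout, 93 × 0.9 = 83.7, so about 84 per arm are evaluable.

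**2. How often a trigger could fire by chance.** The document gives no criterion. If inconsistent is assumed to mean P < 0.05 on any of k independent baseline tests, the probability is 1 − 0.95^k: 9.8% for k = 2, 22.6% for k = 5, 40.1% for k = 10. Both the threshold and k are assumptions.

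**3. Type I error and power by simulation.** There were 168 evaluable patients (84 per arm) and 6,000 replicates per scenario. Sex and age were the covariates, and the trigger was P < 0.05 on either. Prognostic effects are assumed, since the document gives none. Monte Carlo standard error is about 0.3 points near 5% (√(0.05×0.95/6000)) and 0.5 points near 80% (√(0.8×0.2/6000)).

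| Assumed log-odds effect: sex; age per SD | 0; 0 | 0.7; 0.4 | 1.4; 0.7 |
|---|---|---|---|
| No treatment effect: unadjusted | 5.4% | 5.0% | 5.3% |
| No treatment effect: always adjusted | 5.2% | 5.0% | 5.2% |
| No treatment effect: trigger followed mechanically | 5.4% | 4.8% | 4.9% |
| No treatment effect: smaller P reported | 5.7% | 6.2% | 7.2% |
| Planned effect: unadjusted | 77.7% | 78.6% | 77.5% |
| Planned effect: trigger followed mechanically | 77.5% | 78.8% | 78.8% |
| Planned effect: always adjusted | 77.5% | 80.7% | 84.3% |

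The smaller-P row allows the choice in every simulated trial, whether or not imbalance appeared. It is therefore an upper bound for a choice confined to triggered trials.

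**4. Precision by a simpler route.** Prognostic covariates with explained variance R² act roughly like raising n to n/(1 − R²). At 84 per arm, unadjusted power is 78.2%. For R² of 0.02, 0.05, 0.10 and 0.20 it becomes about 79.1%, 80.3%, 82.4% and 86.6%. The gain is nil at R² = 0 and 86.6 − 78.2 = 8.4 points at 0.20.

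**The case against.** The strongest reply is that the primary test is already fixed. Both the Sample size and Statistical analysis sections name the chi-square test, and the disputed sentence does not say that anything replaces it. The natural reading is an unadjusted default with optional supporting analyses. That default is valid in a randomized trial, and adjustment is a gain in efficiency, not a condition of validity. This stands. A reader might infer that the primary result depends on a choice made after outcomes are seen, but the document gives no such timing and never says that the adjusted result would take over. What remains is that it does not rule this out.

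Second, the statisticians are stated to be blinded. That limits steering towards a favoured arm. It does not settle which analysis leads, because both P values can be seen under masked labels.

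Third, a reader might infer that the rule itself inflates type I error, or that imbalance goes uncorrected unless it reaches P < 0.05. The simulation contradicts the first, and the second supplies a threshold that the sentence does not contain.

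Fourth, the section headed Plans for communicating important protocol amendments mentions an approved statistical analysis plan, which is not shown. It may well list covariates and a model, so their absence here is not the point. The point is the conditional rule that the protocol does state.

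**Conclusion.** The concern holds as a fault in a stated rule. Adjustment is tied to observed imbalance, inconsistency is undefined, action is optional, subgroup analysis is offered as a remedy that it cannot be, and the rank of a triggered result is left open.

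The size is modest. There is no type I error inflation if the rule is followed mechanically, and at most about 6% to 7% if results were picked by significance where sex and age are prognostic; the protocol does not propose such picking. The trigger recovers little of whatever precision the covariates offer: in the strongest assumed scenario, 78.8% power against 84.3% with adjustment fixed in advance. It would go too far to say that the plan does lose precision. The documents give no prognostic strength for sex, age or grade, so the supportable statement is that it may forgo between nil and about 8 power points (R² of 0 to 0.20, 84 per arm).

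**What to change.** Delete the imbalance trigger and the subgroup analysis attached to it. In its place, state that:

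- urinary retention will be analysed with adjustment for sex and age, and for hemorrhoid grade (III versus IV) if recorded, whatever the observed balance;
- the method is, for example, logistic regression with a standardized risk difference and 95% confidence interval;
- the unadjusted chi-square test will be reported alongside;
- one of the two is primary, as declared before unblinding.

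Grade carries a condition because it is part of eligibility but is not among the items listed for the baseline form.

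The planned 186 patients and the conduct of the trial do not change. The cost is a small amount of extra analysis and an amendment, which the protocol says must go to ethics review. Recruitment was under way at publication, so the change should be dated and made before unblinding.
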